## Standard Operating Procedure for Problematic Situations

Any subjects presenting with problematic situations will be immediately transferred back to the treating hospital and formally withdrawn from the study

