### *Clinically Emergent Patient Condition*

Should a matter be emergent (that is, requiring in-person assistance in less than 15 minutes), then 9-1-1 will be called and the patient will be returned to the hospital immediately. An example of an emergent patient condition is severe new-onset shortness of breath.

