### *Clinically Urgent Patient Condition*

Should a matter be urgent (that is, a condition that does not require assistance in under 15 minutes), the patient and/or nurse and/or physician may choose to communicate via phone or video (either of the 3 persons can initiate either medium). If this is unsuccessful, the nurse and/or physician will visit the

patient in their home. If there is no way to rectify the situation, then the patient will be transported to the hospital. An example of an urgent situation is new-onset non-severe pain.

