### *Unsafe Home Situation*

Should an unsafe home situation be discovered during a home hospital admission, the home hospital team will assess if said situation poses a harm or threat to either the participant or the home hospital personnel. If it does, and after an attempt to rectify said situation, the situation persists, then the home hospital team will end the study and return the patient to the hospital. An example of an unsafe home situations includes lack of basic sanitation.

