### *Refusal of care*

Should an enrolled subject refuse standard care at their home despite a clear discussion with the home hospital team, then the subject will be transferred back to the treating hospital and formally withdrawn from the study.

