### *Remote vs In-Person Physician Care*

In a randomized controlled non-inferiority trial, we will test an in-person daily physician visit (“in-person care;” control) vs a daily physician visit conducted remotely via video facilitated by a care team member (“remote care;” intervention) for acutely ill patients who are home hospitalized. The primary outcome (dependent variable) is number of adverse events during the acute episode of care (see “Summarizing Adverse Events” table below). The primary predictor (independent variable) is study arm (in-person care vs remote care). We will assess the non-inferiority of the primary outcome with a generalized linear model using Poisson distribution, given the primary outcome is count data. Although we have multiple covariates of interest, we are cognizant of over adjustment. We plan to adjust for age, gender, race/ethnicity, PRISMA-7, education, and HOSPITAL score). We may include additional covariates if groups have significant differences at baseline.

Because patients in the intervention arm will receive at least some of their intervention through a “change agent” (in this case, a Home Hospital team) shared with other participants, we need to account for this in the analysis. We will therefore cluster by Home Hospital physician using general estimating equations.

Other outcomes will be analyzed in a similar manner, using Poisson regression for other “count” outcomes (e.g., number of new or worsening signs or symptoms per patient, days at home since discharge), multivariable logistic regression for binary outcomes (e.g., 30-day readmission, ED visit, PCP

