#### Summarizing Adverse Events

| Measure                                     |
|---------------------------------------------|
| Fall                                        |
| Delirium                                    |
| Potentially preventable VTE                 |
| New pressure ulcer                          |
| Thrombophlebitis at peripheral IV site      |
| CAUTI                                       |
| New Clostridium difficile                   |
| New MRSA                                    |
| New arrhythmia                              |
| Hypokalemia                                 |
| Acute kidney injury                         |
| Transfer back to hospital                   |
| Mortality (unplanned) during admission      |
| Mortality (unplanned) 30-day post-discharge |

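### Patients returned to hospital are formally withdrawn from the study, although the transfer and what follows it belong to the outcomes, so later events, costs and 30-day data may be lost

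*Protocol*

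**What the plan says.** The section Standard Operating Procedure for Problematic Situations opens with a rule that has no exceptions: "Any subjects presenting with problematic situations will be immediately transferred back to the treating hospital and formally withdrawn from the study". Its subsections differ in what they add:

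- Clinically Emergent Patient Condition: "the patient will be returned to the hospital immediately". Withdrawal is not mentioned.
- Clinically Urgent Patient Condition: remote contact first, then a home visit, and only then "If there is no way to rectify the situation, then the patient will be transported to the hospital". Withdrawal is not mentioned.
- Unsafe Home Situation: after an attempt to put things right, "then the home hospital team will end the study and return the patient to the hospital". The subsections on intoxication and on neglect or child abuse use the same closing wording.
- Refusal of care: "then the subject will be transferred back to the treating hospital and formally withdrawn from the study". This is the only subsection that repeats formal withdrawal.

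The primary outcome of the randomised comparison is the "number of adverse events during the acute episode of care" (Remote vs In-Person Physician Care). The table Summarizing Adverse Events lists both "Transfer back to hospital" and "Mortality (unplanned) 30-day post-discharge" among its components. The data-collection tables schedule cost, readmission, mortality and patient experience at 30 days. Nowhere does the protocol say that a patient withdrawn under this procedure stays in follow-up.

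**The concern.** The rule merges two things: the end of home treatment and the end of study participation. Deterioration can trigger it, so the patients it removes are selected on outcome.

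Two comparisons are exposed. In the randomised non-inferiority trial, the arm with more deterioration would have more of its patients' later events cut off, which pulls the arms together and favours a finding of non-inferiority. In the home versus traditional hospital comparison, whose primary endpoint is the cost of the acute episode, only home patients can be withdrawn in this way, and they are plausibly expensive ones. Losing their return stay, or losing them altogether, would make home care look cheaper than it is.

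**Working it through.** No stated figure is in dispute. The check sets the sections side by side and then sizes the exposure.

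**What survives a transfer and what is at risk**

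- *The transfer itself* survives. The Safety table gives it a source (research assistant via physician or nurse) and a time (discharge), the adverse-event table counts it, Safety monitoring sends it to the committee, and the appendix reports it.
- *Later adverse events* (for example delirium or kidney injury in the return stay) are at risk, because they occur after formal withdrawal.
- *Acute-episode cost* is at risk. Its only listed source is home hospital accounting; the system-wide data source is listed for the 30 days after discharge. No source is named for the inpatient stay that follows a transfer.
- *30-day outcomes* are partly at risk. Thirty-day mortality comes from a patient or caregiver call and the experience measures come from the patient. Readmission starts from a patient call but is cross-checked against system data, so it is better protected.
- *The interim look* (Power analysis, remote versus in-person) is taken after 130 patients have completed the study. On a plain reading, a withdrawn patient is not a completer.

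**How many patients**

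The appendix table of safety data shows 5 transfers among 203 home patients.

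- Rate: 5/203 = 0.0246, or 2.5%; exact 95% CI 0.8% to 5.7%.
- Per arm of 130: 130 × 0.0246 = 3.2, range about 1 to 7 over the interval.
- Both arms: 260 × 0.0246 = 6.4.

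**Effect on the randomised comparison (illustration)**

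Assume a control mean of 0.09 events (the planning value), a control transfer rate of 0.0246, and two events per transferred patient (the transfer and one later event). Assume also the same mean among non-transferred patients in both arms:

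(0.09 − 2 × 0.0246) / (1 − 0.0246) = 0.0418.

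With remote-arm transfer rate t:

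- Full remote mean = 2t + (1 − t) × 0.0418, compared with 0.09.
- If later events are lost, remote mean = t + (1 − t) × 0.0418, compared with 0.0246 + 0.9754 × 0.0418 = 0.0654.

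| Remote transfer rate | True difference | Later events lost | Transferred patients excluded |
|---|---|---|---|
| 2.5% (equal to control) | 0 | 0 | 0 |
| 5% | 0.050 | 0.024 | 0 |
| 10% | 0.148 | 0.072 | 0 |

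The margin is 0.1. At 5%, inside the observed interval, the difference is roughly halved but never reaches the margin. A true breach is masked at 10%, which lies above the upper limit of 5.7%.

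**Effect on mean home cost (illustration)**

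Let w be the share transferred and k the cost of a transferred patient relative to a non-transferred one. The documents give no k, so 2 to 4 is an assumption. The fall in mean home cost if these patients are excluded is 1 − 1/((1 − w) + wk). At w = 0.0246:

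- k = 2: 1 − 1/1.0246 = 2.4%
- k = 3: 1 − 1/1.0493 = 4.7%
- k = 4: 1 − 1/1.0739 = 6.9%

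Over the interval for w, the range is 0.8% (w = 0.0080, k = 2) to 14.5% (w = 0.0565, k = 4). The primary aim is a 20% reduction.

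**The case against.** The strongest reply is that loss is inferred. The protocol never says that data are discarded or that follow-up stops at withdrawal. Transfers were counted in the earlier cohort, with those patients kept in the denominator of 203, and some later outcomes can be read from system data without contact. All of this stands, and it limits the point to what may be lost after the transfer.

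Three stronger readings are tempting and not supported:

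- A reader might divide 0.0246 by 0.09 and infer that about 27% of expected events vanish. That assumes the transfers themselves go uncounted, contrary to the adverse-event table and the appendix. It also mixes two cohorts: 0.09 comes from the prior randomised trial, and the protocol does not say whether it includes transfers.
- A reader might take it as established that the trial is biased towards non-inferiority. Each transferred patient already adds one event to the assigned arm, and only a between-arm difference in what follows produces bias. At the observed rate, one later event lost per transferred patient is about 0.025 events per patient in each arm, which cancels if the rates are equal.
- A reader might state that savings are overstated. That needs the return-stay costs to be missed or the patients excluded, and neither is stated.

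It is also fair to say that the analysis set may be defined in an analysis plan that is not shown. That does not answer the point. The withdrawal sentence governs conduct, and no analysis plan can recover data that staff stopped collecting.

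**Conclusion.** The point holds as an inconsistency in a stated rule, and it should be fixed. Followed literally, the opening sentence ends participation at an event that is part of the primary outcome, before other components and all 30-day measures are due. Any resulting loss is informative.

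The expected size is modest: about 2.5% of patients, or 3 per arm. The halving of a between-arm difference rests on one later event per transferred patient, and the 2.4% to 6.9% cost effect on the assumed multiplier and on exclusion. The documents do not show that loss occurs, only that the text permits it.

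A second inconsistency sits in the same section. The opening sentence requires immediate transfer in every case, while the subsections on urgent conditions, unsafe homes and intoxication describe attempts to resolve the situation first.

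**What to change.** Separate the end of home care from withdrawal from the study:

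- Where the text now reads "Any subjects presenting with problematic situations will be immediately transferred back to the treating hospital and formally withdrawn from the study", "then the subject will be transferred back to the treating hospital and formally withdrawn from the study" or "then the home hospital team will end the study and return the patient to the hospital" (and the matching sentences under intoxication and neglect), replace the parts on withdrawing the patient or ending the study. State that home hospital care ends and the patient remains in the study.
- Continue adverse-event, cost and 30-day collection after the transfer, and name a cost source for the return inpatient stay.
- Keep these patients in their assigned group and in the 130 counted for the interim look.
- Reserve withdrawal for withdrawn consent.

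The clinical transfer procedures are for the sponsor. The opening sentence and the subsections need to be reconciled on whether transfer is immediate; no view is offered here on which is right.

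The cost is mainly protocol wording. The research assistant already collects most of these items from the health record, system data and the 30-day call. The one addition is a cost source for the return stay.

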### *Clinically Emergent Patient Condition*

Should a matter be emergent (that is, requiring in-person assistance in less than 15 minutes), then 9-1-1 will be called and the patient will be returned to the hospital immediately. An example of an emergent patient condition is severe new-onset shortness of breath.

### *Clinically Urgent Patient Condition*

Should a matter be urgent (that is, a condition that does not require assistance in under 15 minutes), the patient and/or nurse and/or physician may choose to communicate via phone or video (either of the 3 persons can initiate either medium). If this is unsuccessful, the nurse and/or physician will visit the

patient in their home. If there is no way to rectify the situation, then the patient will be transported to the hospital. An example of an urgent situation is new-onset non-severe pain.

### *Unsafe Home Situation*

Should an unsafe home situation be discovered during a home hospital admission, the home hospital team will assess if said situation poses a harm or threat to either the participant or the home hospital personnel. If it does, and after an attempt to rectify said situation, the situation persists, then the home hospital team will end the study and return the patient to the hospital. An example of an unsafe home situations includes lack of basic sanitation.

### *Intoxication*

Should intoxication occur in the home of a participant, the home hospital team will assess if said intoxication poses a harm or threat to either the participant or the home hospital personnel. If it does, and after an attempt to rectify said intoxication, the situation persists, then the home hospital team will end the study and return the patient to the hospital.

### *Neglect or child abuse*

Should neglect or child abuse be observed, the home hospital team will act as mandatory reporters. The home hospital team, in coordination with the hotline team, will assess if said neglect or child abuse poses an immediate harm or threat to either the participant, children in the home, or the home hospital personnel. If it does, then the home hospital team will end the study and return the patient to the hospital.

### *Refusal of care*

Should an enrolled subject refuse standard care at their home despite a clear discussion with the home hospital team, then the subject will be transferred back to the treating hospital and formally withdrawn from the study.

## BIOSTATISTICAL ANALYSIS

### Specific data variables being collected

Please see above.

### Study endpoints

| Study                                 | Type                                                                         | Primary                    | Secondary                                                                                                         |
|---------------------------------------|------------------------------------------------------------------------------|----------------------------|-------------------------------------------------------------------------------------------------------------------|
| Home hospital vs traditional hospital | Prospective intervention group, retrospective propensity-weighted evaluation | Cost of acute care episode | Cost of acute care episode and 30 days post-discharge
Length of stay
Unplanned readmission after index, y/n |

|                                                         |                                                                              |                                                       |                                                                                                                                   |
|---------------------------------------------------------|------------------------------------------------------------------------------|-------------------------------------------------------|-----------------------------------------------------------------------------------------------------------------------------------|
|                                                         |                                                                              |                                                       | Number of adverse events
Picker experience questionnaire                                                                       |
| Remote vs in-person home hospital physician             | RCT, non-inferiority                                                         | Number of adverse events                              | Unplanned readmission after index, y/n
Picker experience questionnaire
Global experience score                              |
| Early transfer to home hospital vs traditional hospital | Prospective intervention group, retrospective propensity-weighted evaluation | Cost of acute care episode and 30 days post-discharge | Unplanned readmission after index, y/n
Picker experience questionnaire
Global experience score
Number of adverse events* |
| Paramedic + nurse care vs nurse care alone              | Retrospective, non-inferiority, propensity-weighted evaluation               | Number of adverse events                              | Unplanned readmission after index, y/n
Picker experience questionnaire
Global experience score
Personnel costs           |

\*Non-inferiority for this outcome

## Statistical methods

### *Home hospital vs traditional hospital*

#### *Quantitative*

We plan to form 3 different control groups (with groups listed in order of preference):

1. Patients who were deemed eligible for home hospital, but the service was full (and they were not enrolled subsequently if the service was no longer full);
2. Patients who were deemed eligible for home hospital, but lived outside of the 7.5-mile catchment area; and
3. Patients who were admitted to the hospital.

For each control group, we will use propensity score weighting, adjusting for covariates of interest (see table above), baseline functional status, and DRG. We will be cognizant of over-adjustment depending on our final sample size for each group above. If possible, we will use only group 1 above, as it is the strongest. If we have insufficient control group sample size, we may choose to combine groups 1 and 2 above.

The primary outcome (hospitalization cost) will be assessed using a generalized linear model assuming a gamma distribution with a log link. We will use a multivariable regression approach for secondary

outcomes, using logistic regression for binary outcomes and non-transformed linear regression for normally distributed continuous outcomes as appropriate.

We *a priori* plan to perform a subgroup analysis that does not involve any outlier participants, should this occur. We also *a priori* plan subgroup analyses by diagnosis, by age group, by disposition, by location of admission (e.g., ED, floor, clinic, and home), and by daily activity level. We also *a priori* plan to analyze our outcomes with means, but also with median and interquartile ranges, which are less subject to outlier effects. We may choose to employ non-parametric tests of significance should our data be nonparametric.

We *a priori* plan to adjust our secondary analyses using the Benjamini-Hochberg method. We *a priori* choose a false-discovery rate of 0.20.

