## BACKGROUND AND SIGNIFICANCE

### Historical background

Hospitals are the standard of care for acute illness in the US, but hospital care is expensive and often unsafe, particularly for older individuals. While admitted, 20% of older adults suffer delirium, over 5% contract hospital-acquired infections, and most lose functional status that is never regained. Timely access to inpatient care is poor: many hospital wards are typically over 100% capacity, and emergency department waits can be protracted. Moreover, hospital care is increasingly costly: many internal medicine admissions have a negative margin (i.e., expenditures exceed hospital revenues) and incur patient debt.

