Of importance, we have chosen to add 3 diagnoses (acute pancreatitis, inflammatory bowel disease exacerbation, and cystic fibrosis exacerbation) to this protocol that were originally planned to be randomized in our randomized controlled protocol (2016P001337). Due to volume constraints (high volumes of current diagnoses coupled with no budgeted ability to expand staff) we have not been able to start to care for these 3 new diagnoses but have carefully noted that we would be unlikely to enroll sufficient patients to make a RCT meaningful for these new diagnoses. We do now have the ability to hire additional staff members, allowing us to expand to these new diagnoses. We still believe that home hospital care could benefit these patients and want the opportunity to care for them. We will continue to closely vet each case for any safety issues and have any issues reviewed by our safety review committee as per our current protocol. With the IRB’s approval, we will therefore move these diagnoses to the present protocol. We will continue to maintain protocol 2016P0001337 for bariatric surgery, as we are confident we can enroll a sufficient volume.

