- For atrial fibrillation with rapid ventricular response
  - Likely to require cardioversion
  - New atrial fibrillation with rapid ventricular response
  - Unstable blood pressure, respiratory rate, or oxygenation
  - Despite IV beta and/or calcium channel blockade in the emergency department, HR remains > 125 and SBP remains different than baseline
  - Less than 1 hour of time has elapsed with HR < 125 and SBP similar or higher than baseline
- For patients with end-stage renal disease on peritoneal dialysis
  - Peritoneal catheter malfunction
  - Requires temporary hemodialysis
- For exacerbation of IBD
  - Fever > 102F
  - Rigid/surgical abdomen
  - Acute intestinal obstruction, perforation, or toxic megacolon
  - History of intestinal obstruction, perforation, toxic megacolon
  - Abscess or abdominal mass
  - Likely to require total parenteral nutrition
  - Likely to require blood transfusion
- For acute pancreatitis
  - Please refer to attachment
- For exacerbation of cystic fibrosis or non-cystic fibrosis bronchiectasis
  - Pneumonia criteria above
  - Respiratory failure
  - Moderate or large-volume hemoptysis ( $\geq 10\text{mL}$ )
  - Pneumothorax
  - Pancreatitis
  - Post-transplant
- Home hospital census is full (maximum 16 patients at any time)

\*GWTG-HF: AHA Get with the Guidelines: SBP, BUN, Na, Age, HR, Black race, COPD  
 ADHERE: Acute decompensated heart failure national registry: BUN, creatinine, SBP

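### The preferred control group arises only when the home service is full, but the stated propensity set has no calendar or season term, so the primary cost comparison may be confounded by when patients presented

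*Protocol*

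**What the plan says.** The Quantitative part of the protocol's Statistical methods for home hospital vs traditional hospital lists three control groups in order of preference. Group 1 is "Patients who were deemed eligible for home hospital, but the service was full", provided that "they were not enrolled subsequently if the service was no longer full". Group 2 is eligible patients living outside the catchment area, and group 3 is patients admitted to the hospital. On the choice among them it says: "If possible, we will use only group 1 above, as it is the strongest". If group 1 is too small, "we may choose to combine groups 1 and 2 above".

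The exclusion criteria define a full service as 16 patients.

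For each control group, "we will use propensity score weighting, adjusting for covariates of interest (see table above), baseline functional status, and DRG". The Covariates of Interest table holds patient-level items: demographic and social factors, comorbidities, prior use of care, frailty, code status and InterQual levelling. It has no admission date, season or calendar period.

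The primary outcome is the cost of the acute episode, analysed with a gamma model and log link. The primary aim is a 20% reduction. The Early transfer section foresees a variable recording that a patient was first turned away because the census was full; the main cost comparison has nothing comparable.

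**The concern.** Take two eligible patients in the catchment who would both accept home hospitalization. What separates the home patient from the group 1 control is the home census at presentation, and that census follows demand over time. Group 1 controls accrue only while the service is full, and home patients only while a slot is open. If full periods cluster in certain seasons or years, the two groups will be distributed differently over the calendar.

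That matters only if the cost of an episode also varies over the calendar among patients alike on the adjusted covariates. This is plausible: the included conditions contain pneumonia, COPD/asthma, heart failure and other infection, and prices change from year to year. The log-link model reads any such difference as a proportional effect of home care. With the aim stated as a fixed 20% reduction, a bias of several percentage points could decide whether the aim appears to be met.

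**Working it through.** **No stated figure to reproduce.** The point rests on how group 1 is defined and on the adjustment list, not on a number in the protocol. The 144 patients per arm for a $1000 difference cannot be reproduced independently, because the cost SD is not given.

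**Step 1: the two passages side by side.** Membership of group 1 is set by the census at presentation. The adjustment list is explicit, and none of its items records when the patient presented. Followed as written, the weighting balances patient characteristics but not timing.

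**Step 2: possible size with partial overlap in time.** All inputs are assumptions.

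- r = cost in peak periods divided by cost at other times, for comparable patients
- q0 = share of home patients presenting in peak periods, set at 0.25
- q1 = share of group 1 controls presenting in peak periods, 0.50 to 1.00

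With no true effect of home care, the spurious home-to-control cost ratio is [1 + q0(r − 1)] / [1 + q1(r − 1)].

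| r | q1 = 0.50 | q1 = 1.00 | Spurious saving |
|---|---|---|---|
| 1.05 | 1.0125/1.025 = 0.988 | 1.0125/1.05 = 0.964 | 1.2% to 3.6% |
| 1.10 | 1.025/1.05 = 0.976 | 1.025/1.10 = 0.932 | 2.4% to 6.8% |
| 1.20 | 1.05/1.10 = 0.955 | 1.05/1.20 = 0.875 | 4.5% to 12.5% |

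**Step 3: the opposite direction.** If peak periods cost less by the same factors (r = 1/1.05 to 1/1.20), the same formula gives ratios from 1.012 (r = 1/1.05, q1 = 0.50) to 1.15 (r = 1/1.20, q1 = 1.00), which hides a real saving. Likewise, if controls accrued on average one year earlier and costs rose 3% to 5% a year (assumed), the ratio with no true effect would be 1.03 to 1.05.

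**Step 4: what a residual gap does to the test.** Assume a two-sided 0.05 test and a normal approximation. Solving the 144 per arm backwards gives SD = 1000 × √(144/2) / (1.960 + 1.282) ≈ $2,618. The standard error of the difference is 2,618 × √(2/144) ≈ $309. With no true effect, an unadjusted timing gap of $250 (250/309 = 0.81 standard errors) raises the false-positive rate from 5% to 13%, and a gap of $500 (1.62 standard errors) raises it to 37%. This ignores the weighting and the gamma model, so it shows sensitivity and does not forecast the error rate.

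**The case against.** The strongest reply is that the protocol contains no evidence that time affects cost once the listed covariates are held fixed. DRG, comorbidities and InterQual levelling absorb part of any seasonal shift in case mix or severity. Groups 2 and 3 are also planned, and their membership does not depend on the service being full. An SAP, not shown, could add time terms. All of this limits the point. It does not remove it: the protocol prefers group 1 alone and names its adjustment list, and patient-level covariates do not record price year.

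A reader might go further in four ways that the documents do not support.

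- *The effect is confounded.* Confounding needs an effect of time on cost given the covariates, and no data on this are given. Only the possibility is supported.
- *The spurious saving is 5% to 17%.* That comes from 1 − 1/(1 + x), with x = 0.05, 0.10 and 0.20 giving 4.8%, 9.1% and 16.7%. It puts every control and no home patient in a peak period. Slots open and close, so home and control patients can present in the same week or even on the same day.
- *A full home service means a crowded hospital.* The protocol's remark that "many hospital wards are typically over 100% capacity" is general background and, if anything, suggests constant crowding. It does not show that ward care costs more when a 16-patient home service is full.
- *The share of full days has drifted.* The Rationale says "We do now have the ability to hire additional staff members, allowing us to expand to these new diagnoses", and the 5-mile radius belongs to the earlier randomized trial. Neither shows that the frequency of full days changed during the period to be analysed.

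**Conclusion.** The point holds in a limited form. The preferred control group is defined by a condition that varies over time, and the stated adjustment set has no term for time. The primary cost comparison may therefore be confounded by season or calendar period. Direction and size are unknown. Under the assumed overlap and peak costs 5% to 20% higher, the spurious saving is about 1% to 12%; under the reverse assumptions a true saving is understated. These ranges rest wholly on assumed values of r, q0 and q1, and they make no allowance for what DRG, comorbidities and severity levelling would remove. That is enough to justify a nearly free correction before the control data are assembled, but not a claim that the result will be biased.

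**What to change.** In the Quantitative paragraph on control groups:

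- Add admission calendar period (quarter, or month plus year) to the propensity model for every control group.
- Express all costs in constant dollars.
- Report group 2, drawn from the same calendar periods as the home patients, as a sensitivity comparison, because its membership does not depend on the service being full.

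In the Early transfer section, add the same calendar term alongside the full-census variable already foreseen there.

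Do not put fullness of the home service into the main propensity model. It defines group 1, so there would be no overlap to weight on. Hospital occupancy appears in none of the data tables; it could serve as a sensitivity covariate if it can be retrieved.

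Cost: admission dates are already on record, so the calendar term needs no new data collection. Weights will be somewhat larger, and some precision is lost where home and control patients overlap little in time.
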